#### 10.1 Primary study parameter(s)

Per (newly developed) scoring criteria the reduction of (positive) SNLB procedures will be calculated as well as the number of unnecessary neck dissections (accompanying false positives).

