#### 4.4 Sample size calculation

Since it is unlikely that FDG-PET/CT will detect micrometastases with a sensitivity high enough to refrain from (elective) neck dissection if FDG-PET/CT is negative, the focus of this study will be on a PPV high enough to avoid SLNB with second stage neck dissection if FDG-PET/CT is positive. The sample size calculation is made on the number of early-stage OSCC patients, who undergo FDG-PET/CT, needed to reduce reliably the number of (positive) SLNB procedures by 25%.

Unfortunately, no studies with histopathological examination of neck dissection specimens or SLNB and follow-up as reference standard are available which vary cut-off values of objective scoring parameters, e.g. SUVmax, to find a high PPV for the detection of occult lymph node metastases. All such studies focused on a high sensitivity or the combination of sensitivity and specificity, whereas for the present study particularly a high PPV is needed. The study of Peltenburg et al compared SUVmax and lymph node size with the outcome of USgFNAC (14). Although the sensitivity of USgFNAC is limited, its specificity is near 100%. In 52 patients with lymph nodes smaller than 10 mm (radiologically negative) SUVmax was >4.9 in 17 patients of whom 12 had USgFNAC positive lymph nodes. Thus, if patients with SUVmax >4.9 would undergo directly a neck dissection in at least 12 patients a SLNB (with neck dissection as a second stage operation if SLNB is positive) could correctly be avoided. Using this SUVmax cut-off value a reduction of SLNB of 32.7% can be obtained and only a few unnecessary neck dissections will be performed.

To show with an 80% power and a one-sided alpha of 0.05 that the reduction of SLNB of 0.327 is not inferior to 0.25, we need 143 patients. This sample size was calculated using the PASS power software, option: non-inferiority test for one proportion, exact test.

As explained before it is expected that 4.2% of patients have to be excluded because of positive USgFNAC after to FDG-PET/CT. Further drop-out rate for this study is expected to be 5%. After all, generally, patients want to have an extensive diagnostic work-up. FDG-PET/CT is a routine diagnostic examination with a limited burden on the patient. Therefore, a total drop-out rate of (not more than) 10% is expected. Accordingly, this study's population should consist of 159 patients to enable sufficient statistical power.

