### **FDG-PET/CT scoring parameters**

Models based on combinations of FDG-PET/CT parameters will be constructed and analysed for accuracy. The accuracy of scoring parameters will be analysed for a wide range of cut-off values for each parameter, through which sensitivity, specificity, positive predictive value, and negative predictive value will vary, allowing for choosing the optimal results for the specific aim of this study: a high positive predictive value (PPV) to reduce the number of SLNBs with acceptable sensitivity.

We will first compare the different scoring results (visual, semi-quantitative) and the morphology characteristics of the patients with and without metastases (based on the reference standard of SLNB and/or 12-month follow-up). Comparison of continuous data will be expressed as differences in mean  $\pm$  standard deviation (SD) when normally distributed, and as median  $\pm$  interquartile range (IQR) when skewed. Univariate analysis using independent samples T-tests will be applied for parametric continuous variables, while Friedman's 2-way ANOVA's and Wilcoxon signed rank tests will be applied for non-parametric continuous variables. Comparison of categorical variables will be expressed as differences in proportions. For comparing categorical data  $\chi^2$ -tests will be used.

Searching for the optimal cut-off values and subsequently assessing performance at these cut-off values within the same dataset can result in an overly optimistic estimation of performance as described by Leeflang et al (22).

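### Section 10.1 names no criterion for the 0.25 comparison on which section 4.4 sizes the trial, and nothing corrects for choosing the criterion and cut-off in the same data

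*Protocol*

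**What the plan says.** Section 4.4 builds the sample size on one comparison: "To show with an 80% power and a one-sided alpha of 0.05 that the reduction of SLNB of 0.327 is not inferior to 0.25". The method is given as "non-inferiority test for one proportion, exact test", with the conclusion that "we need 143 patients". The expected value of 0.327 comes from a cited study at one SUVmax cut-off (above 4.9), which 17 of 52 patients exceeded.

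Section 10.1 is one sentence: "Per (newly developed) scoring criteria the reduction of (positive) SNLB procedures will be calculated", together with the number of unnecessary neck dissections. The value 0.25 does not appear anywhere in section 10. The opening of section 10 gives a general p<0.05 rule without sidedness or hypothesis.

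The candidates are many. Section 8.1.2 lists a Likert scale, the Hopkins criteria, six SUV metrics, lesion-to-background ratios and morphology. Section 10.2 (FDG-PET/CT scoring parameters) adds combined models and says that accuracy "will be analysed for a wide range of cut-off values for each parameter", so that the best result for high PPV with acceptable sensitivity can be chosen. It then acknowledges that choosing and assessing cut-offs in one dataset gives over-optimistic performance, and stops there.

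**The concern.** The sizing and the primary analysis are different in kind. One is a single confirmatory test of one proportion. The other is a list of calculated reductions, one for each criterion developed in the same patients. Someone writing the analysis from this protocol could not tell which criterion is to be compared with 0.25.

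Two things are at stake. First, the claim that the trial is sized to make has no designated answer. Second, the PPV and the reduction reported for the chosen criterion come from the data that chose it, so they will tend to look better than they would in new patients. The reduction also needs PPV beside it. As section 4.4 computes it, the reduction is simply the share of patients above the cut-off, so a lower cut-off raises it automatically.

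**Working it through.** **Inputs from section 4.4.** Threshold 0.25; expected reduction 0.327; one-sided alpha 0.05; power 80%; exact one-proportion test; 143 evaluable; 10% drop-out; 159 enrolled.

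**1. The plan's own figures.**
- Expected reduction: 17/52 = 0.327. This reproduces. It counts all 17 patients above the cut-off, 5 of whom (17 − 12) were not USgFNAC-positive.
- Enrolment: 143/0.9 = 158.9, rounded up to 159. This reproduces.
- Evaluable number: find the smallest r with P(X ≥ r | n, 0.25) ≤ 0.05; power is P(X ≥ r | n, 0.327). At n = 143, P(X ≥ 44) = 0.070 and P(X ≥ 45) = 0.048, so success needs 45/143 (31.5%). Power at 0.327 is 0.653. The 143 does not reproduce. The smallest n with 80% power is 219 (r = 66, power 0.810), and power stays at or above 80% from n = 235.
- The matching one-sided 95% exact lower bound is 0.251 at 45/143 and 0.244 at 44/143, so the test and the bound agree.

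**2. If the largest reduction is the one set against 0.25.** Assumptions, none of them from the protocol: k = 5, 10 or 20 criteria; every true reduction exactly 0.25; n = 143; equally correlated latent normals cut at a positive share of 25%; success if any criterion reaches 45/143.

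| Latent correlation | k = 5 | k = 10 | k = 20 |
|---|---|---|---|
| 0.8 | about 15% | about 22% | about 30% |
| 0.9 | about 13% | about 18% | about 23% |

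A single fixed criterion gives 4.8%.

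**3. If the criterion with the highest observed PPV is selected, the aim stated in section 10.2.** Same null, with a prevalence of 27% (section 3) and a common true PPV of 0.5 or 0.7 (assumed). Sensitivity is then 0.25 × PPV/0.27 = 0.46 or 0.65. The false-positive rate is 0.25 × (1 − PPV)/0.73 = 0.17 or 0.10. In 8,000 runs per cell, over the same k and correlations, the selected criterion reached 45/143 in about 1-3% of trials. In the same runs at least one criterion did so in roughly 11-28%. Selecting on PPV favours criteria that call fewer patients positive, so on this null it lowers the error on the reduction.

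**4. Safeguards in the text.** LASSO (section 10, Handling missing Data) is said to protect against overfitting, but it concerns the regression model for metastasis. It does not cover the choice among visual, Hopkins and SUV criteria, nor the cut-off. The multistage bootstrap in section 10.2 handles correlation between sides and levels of the same patient's neck. Neither repeats the selection step.

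**The case against.** Section 4.4 already fixes the threshold, sidedness, alpha and test. Section 10.1 is silent on them and does not contradict them, and a separate analysis plan could repeat the test and name the lead criterion. Developing several criteria is a declared aim, so calculating a reduction for each is part of the design. Section 10.2 admits the optimism, and LASSO is named.

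Part of this stands. It would be too strong to say that the sized claim is never tested, since the test is described in section 4.4. What remains is that the protocol does state a primary analysis, and that analysis does not say which criterion the sized comparison belongs to.

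A reader might also infer that the 5% error is inflated to 13-30%. The documents do not support that. Those rates need the largest reduction to be picked, whereas section 10.2 selects on PPV, and under that rule the simulated error on the reduction stays below 5%. The null is also artificial: a true reduction of 0.25 for every criterion cannot hold over a wide range of cut-offs, because moving the cut-off changes the reduction itself.

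Finally, a plain exact test is not a complete remedy. It is not guaranteed to hold 5% for a model and cut-off fitted in the same 143 patients.

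**Conclusion.** The point holds in this form: the comparison that justifies the sample size has no designated criterion in the primary analysis, and the PPV and reduction of the chosen criterion will be reported without correction for selection, although the protocol recognises the problem.

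The amount of optimism cannot be computed from the protocol, because the number of criteria, the cut-off grid and their correlation are not given. Error inflation on the reduction is conditional: about 13-30% if the largest reduction is used, about 1-3% if the highest PPV is used, both under the assumptions stated above.

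The power figure rests only on the protocol's own inputs: 65.3% at n = 143 under the exact test, against the stated 80%. The mismatch between sections 4.4 and 10.1 would remain at any sample size.

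**What to change.** Amend section 10.1, before the scan readings are linked to the reference standard, in one of two ways:

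- **(a)** Name one criterion with a fixed cut-off as primary. Compare its reduction with 0.25 by the exact one-sided 5% test and report the one-sided 95% lower bound. Because the reduction depends on the scan readings alone, the cut-off should also be fixed before those readings are tabulated.
- **(b)** Fix the selection rule in advance (PPV-based, with the acceptable sensitivity stated). Repeat the whole selection, including the cut-off search, inside a bootstrap or cross-validation, and compare the optimism-corrected one-sided 95% lower bound with 0.25.

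In both cases, report the PPV with its interval and the number of unnecessary neck dissections beside the reduction, so that a lower cut-off alone cannot count as success. Report all other criteria descriptively.

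In section 4.4, state that the exact test at n = 143 (success at 45 or more) has about 65% power at 0.327. If 80% is to be kept, 219 evaluable patients are needed (219/0.9 = 243.3, so 244 enrolled), or 235 for power that stays above 80% (235/0.9 = 261.1, so 262 enrolled).

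The analysis changes cost wording and some computing, with no added visit or scan. The downsides are that other criteria cannot be claimed as confirmatory and that corrected figures will be slightly less favourable. Restoring 80% power would cost recruitment; otherwise the lower power has to be accepted openly.

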#### 10.2 Secondary study parameter(s)

##### Accuracy

Analysis of the accuracy of FDG-PET/CT will be performed per patient, per neck side, and neck level (I-V) (as performed by Bae et al (20)). Results of SLNB and follow-up of 12 months will be used as the reference standard.

The most important secondary outcome is the positive predictive value, calculated as the number of positive patients/necks/levels on FDG-PET/CT with histologically confirmed lymph node metastases divided by the total number of patients/necks/levels with a positive FDG-PET/CT.

In addition, sensitivity, specificity and negative predictive value, and the proportion of true positives and false positives will be estimated.

For estimation of 95% confidence intervals, we will use multistage bootstrap to account for the correlation between sides/levels of necks from the same patients, as was described by Lowe et al (21). We will repeat the statistical analysis for a scenario where in clinical practice all positive FDG-PET/CTs would not be followed by SLNB but a neck

dissection at the same operation as the resection of the primary tumor. Such a scenario could be useful to reduce the number of SLNBs and second stage neck dissections.

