With the sample size of 143 patients, we expect 47 patients to have a positive FDG-PET/CT scan. Based on the study of Peltenburg et al, we anticipate 33 positive and 14 negative histopathological examination results (14). This results in a PPV of 0.70. Based on binomial exact calculation of the 95% confidence interval (CI), with 47 patients having a positive FDG-PET/CT and a PPV of 0.70, an associated 95% CI of 0.56-0.84 is

expected.

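### Section 10.2 names a multistage bootstrap for the per-side and per-level intervals; if sides and levels are redrawn inside each patient, those intervals come out too wide, and resampling whole patients avoids this

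*Protocol*

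**What the plan says.** Section 10.2 (Accuracy) analyses FDG-PET/CT at three units: patient, neck side and neck level I to V. PPV is called the most important secondary outcome and is defined at each unit as the confirmed positives "divided by the total number of patients/necks/levels with a positive FDG-PET/CT". Sensitivity, specificity and NPV follow.

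For the 95% intervals the section states: "we will use multistage bootstrap to account for the correlation between sides/levels of necks from the same patients". For the algorithm it refers to a cited multicentre PET/CT trial. It does not give the number of stages, the unit drawn at each stage, or a within-patient correlation.

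Section 4.4 gives the number of patients: "With the sample size of 143 patients, we expect 47 patients to have a positive FDG-PET/CT scan". The only interval it plans is for the per-patient PPV, by an exact binomial method.

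**The concern.** The protocol recognises the clustering and names a method for it. The question is whether that method gives intervals of the right width.

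A bootstrap that resamples whole patients is a one-stage cluster bootstrap. Calling it multistage ordinarily means a further draw inside each selected patient. Two things then go wrong:

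- The variance between patient totals already includes the variation among sides and levels within patients. A second draw adds that component again.
- Left and right, and levels I to V, are all observed in every patient. Drawing them with replacement can give a neck with one side twice and the other never, which is not how the data arise.

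At stake is the reported precision of per-side and per-level PPV, sensitivity, specificity and NPV. Section 10.2 uses these measures to compare scoring criteria.

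**Working it through.** **Plan's own figure.** The protocol states no per-side or per-level interval, width or correlation, so there is nothing to reproduce. Its one planned PPV interval (0.56 to 0.84 for 33 of 47) is per patient and involves no bootstrap.

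**Inputs.** From the documents: 143 patients (Section 4.4), and sides and levels I to V (Section 10.2). Assumed: two sides of five levels each, and replacement sampling at every stage. The within-patient correlation r is not given, so a range is shown.

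**Step 1: simple proportion, uncorrelated units.** Set the variance of one level to 1. For the mean over a patient's ten levels:

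- true variance: 1/10 = 0.10
- added by redrawing 2 sides: a side mean has variance 1/5; the spread between the two sides is 1/5 × 1/2 = 0.10; averaged over two draws, 0.05
- added by redrawing 5 levels within each drawn side: 4/5 ÷ 10 = 0.08

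The total is 0.23, so the SE ratio is √(0.23/0.10) = √2.3 = 1.52. For the per-side analysis (patient, then side) the true variance is 1/2 and the added part 1/4, so the ratio is √1.5 = 1.22.

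**Step 2: with equal correlation r within a patient.**

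- Per side: √{1 + 0.25(1−r) / [r + 0.5(1−r)]}
- Per level, three stages: √{1 + 0.13(1−r) / [r + 0.1(1−r)]}

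| r | per side | per level |
|---|---|---|
| 0 | 1.22 | 1.52 |
| 0.1 | 1.19 | 1.27 |
| 0.3 | 1.13 | 1.12 |
| 0.5 | 1.08 | 1.06 |

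**Step 3: why PPV stays near the upper end.** PPV counts only PET-positive units, and these are few. Take a patient with one PET-positive level. The number of times its side is drawn has mean 1 and variance 2 × ½ × ½ = 0.5. Given the sides drawn, the level draw adds 5 × 0.2 × 0.8 = 0.8. The count therefore has mean 1 and variance 1.3. Drawing patients contributes about 1 more, for a total of 2.3 against 1 when whole patients are drawn: again √2.3 = 1.52. When a patient has several positive levels with the same outcome, the excess is smaller.

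**Step 4: simulation of PPV.** Inputs: 143 patients, 2 × 5 levels, 24% to 27% node-positive with 1 to 3 metastatic levels on one side, per-level sensitivity 0.5 to 0.7, per-level false-positive rate 0.8% to 1.2%, patient random-effect SD 0.3 to 1.5; 120 data sets with 250 resamples each. The node-positive share fits Section 3: 27% prevalence less the 4.2% excluded for positive cytology gives (0.27 − 0.042)/(1 − 0.042) = 0.238. The other rates are assumptions.

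| Resampling | bootstrap SE / true SD |
|---|---|
| Per-level PPV, patient–side–level | 1.35 to 1.48 |
| Per-level PPV, patient–side, levels kept | 1.16 to 1.23 |
| Per-side PPV, patient–side | 1.20 to 1.24 |
| Patients only | 0.96 to 1.00 |

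Mean width of the per-level PPV interval was 0.36 to 0.41 with three stages and 0.25 to 0.28 with patients only. Coverage with three stages was 98% to 100%.

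A second simulation of the same layout, including a large patient effect, gave three-stage to patient-only SE ratios of 1.32 to 1.50 per level and 1.22 to 1.26 per side. One further set gave 1.48 to 1.58 per level and 1.29 per side; the other runs did not reach those values and they are not relied on.

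**Step 5: a milder version.** If levels are drawn directly within patients (two stages, ten levels), the per-level PPV ratio was 1.36, 1.32, 1.18 and 1.08 at latent correlations of 0, 0.2, 0.5 and 0.8. The per-side ratios were 1.23, 1.21, 1.17 and 1.10. Patient-only resampling stayed at 0.91 to 1.04 of the true SD across PPV, sensitivity and specificity.

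**The case against.** **The algorithm is not in the protocol.** Section 10.2 gives a name, a correct purpose and a citation. If the cited trial drew only patients, the intervals are sound and only the word multistage misleads. This stands. A reader might infer that the intervals will be too wide; the documents support only that they would be if the inner stages are redrawn.

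**This is detail for the SAP.** A protocol may leave the interval method open, but this one does not: it commits to a named method whose usual form is unsuitable here. The point concerns that commitment, not missing detail.

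**The size depends on unstated inputs.** This also stands. With strong correlation the excess falls below 10%, and the per-level figure of 1.3 to 1.5 needs all three stages. The limit of √2 = 1.41 that applies to a two-stage scheme does not cap a three-stage one, as Step 1 shows.

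**The consequences are small.** A reader might infer that a good scoring criterion could fail because of this, or that the decision to omit SLNB is affected. The documents do not support either. Sections 10.1 and 10.2 attach no PPV threshold to an interval limit. The primary endpoint does not use these intervals, and the per-patient PPV has one unit per patient, so there is nothing to redraw inside it.

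**Conclusion.** The concern holds in conditional form. If, as the name ordinarily means, sides and levels are redrawn with replacement within each drawn patient, the method overstates the variance of the per-side and per-level measures. For PPV the intervals would then be about 1.2 times too wide per side and about 1.3 to 1.5 times too wide per level. This assumes 143 patients, two sides of five levels, sparse PET-positive levels and three stages for the per-level analysis. The excess is smaller with fewer stages or stronger within-patient correlation.

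The error is conservative: coverage is above 95%, at the price of precision the data contain. It is confined to secondary per-side and per-level intervals. Confidence is moderate, because the stages are not described in the protocol and the cited trial is not at hand.

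**What to change.** Replace the bootstrap sentence in Section 10.2 with:

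*For per-side and per-level measures, 95% CIs will be obtained by resampling patients with replacement, keeping all sides and levels of each sampled patient (cluster bootstrap).*

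A ratio estimator with patient-clustered robust variance is an acceptable alternative. The change is right whichever algorithm the cited trial used, and it settles the method before analysis. It costs one sentence and simpler code, needs no new data and has no effect on patients or sites.

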### **FDG-PET/CT scoring parameters**

Models based on combinations of FDG-PET/CT parameters will be constructed and analysed for accuracy. The accuracy of scoring parameters will be analysed for a wide range of cut-off values for each parameter, through which sensitivity, specificity, positive predictive value, and negative predictive value will vary, allowing for choosing the optimal results for the specific aim of this study: a high positive predictive value (PPV) to reduce the number of SLNBs with acceptable sensitivity.

We will first compare the different scoring results (visual, semi-quantitative) and the morphology characteristics of the patients with and without metastases (based on the reference standard of SLNB and/or 12-month follow-up). Comparison of continuous data will be expressed as differences in mean  $\pm$  standard deviation (SD) when normally distributed, and as median  $\pm$  interquartile range (IQR) when skewed. Univariate analysis using independent samples T-tests will be applied for parametric continuous variables, while Friedman's 2-way ANOVA's and Wilcoxon signed rank tests will be applied for non-parametric continuous variables. Comparison of categorical variables will be expressed as differences in proportions. For comparing categorical data  $\chi^2$ -tests will be used.

Searching for the optimal cut-off values and subsequently assessing performance at these cut-off values within the same dataset can result in an overly optimistic estimation of performance as described by Leeflang et al (22).

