### Handling missing Data

Missing data will be handled using multiple imputation strategies. Results across multiple imputation data sets will be combined using the Rubin rules. LASSO-based logistic regression analysis will be used to identify the optimal panel for distinguishing patients with metastases from those without. This method is suitable for regression with a large number of variables and a relatively limited number of events and protects against overfitting. To estimate discriminative value we will compute the area under the curve (AUC) of the Receiving Operator Characteristic Curve (ROC).

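### Scoring criteria and cut-offs are chosen for high PPV and assessed in the same patients; the protocol names the optimism but states no correction for PPV and other results based on true positives

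*Protocol*

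**What the plan says.** Section 10.2 (FDG-PET/CT scoring parameters) builds models from combinations of parameters and states that "The accuracy of scoring parameters will be analysed for a wide range of cut-off values for each parameter", so that the best result for high PPV at a tolerable sensitivity can be picked. No numerical target is given for either quantity. The subsection closes with the warning that "Searching for the optimal cut-off values and subsequently assessing performance at these cut-off values within the same dataset can result in an overly optimistic estimation", and nothing follows it.

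Section 10.1 then carries the selected criteria into the primary endpoint: "Per (newly developed) scoring criteria the reduction of (positive) SNLB procedures will be calculated", together with the number of unnecessary neck dissections. Section 10.2 (Accuracy) makes PPV the leading secondary outcome, in the same cohort.

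Two statements could be taken as safeguards. Section 10 (Handling missing Data) says of LASSO: "This method is suitable for regression with a large number of variables and a relatively limited number of events and protects against overfitting". Section 10.2 (Accuracy) plans a multistage bootstrap for confidence intervals, with the stated purpose of handling correlation between sides and levels of the same patient.

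Section 4.4 sizes the study as for one fixed criterion: "the reduction of SLNB of 0.327 is not inferior to 0.25, we need 143 patients", with "an 80% power and a one-sided alpha of 0.05" and the PASS "option: non-inferiority test for one proportion, exact test".

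**The concern.** When the criterion and cut-off with the best observed PPV are picked from many, part of what makes them best is chance in that sample. The same patients then return a PPV that is too high on average, and an interval computed as if the rule had been fixed beforehand is too narrow.

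The search is wide and the information small. Section 8.1.2 lists 6 SUV metrics, lesion-to-background ratios for 2 metrics over about 5 backgrounds, 2 visual scales and 5 morphology features, besides combinations.

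Neither stated safeguard reaches this step. LASSO shrinks coefficients while a panel of variables is chosen. It does not adjust PPV at a cut-off searched afterwards, nor the choice among visual, Hopkins, SUV and morphology criteria. The bootstrap, used as described, resamples around a rule already selected.

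At stake is the main product of the study: a rule proposed for future use in which a positive PET/CT would replace SLNB by direct neck dissection. An inflated PPV understates the unnecessary dissections reported under 10.1 and feeds into the true- and false-positive cost scenarios of the cost-effectiveness analysis.

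**Working it through.** **1. The plan's own figures (section 4.4).** In the earlier study, "SUVmax was >4.9 in 17 patients of whom 12 had USgFNAC positive lymph nodes", out of 52 patients.
- Planned reduction: 17/52 = 0.327. This is the PET-positive share and does not use the reference standard.
- Expected PET-positive: 143 × 0.327 = 46.8, stated as 47.
- Expected true positives: 46.8 × 12/17 = 33. PPV = 33/47 = 0.70.

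These reproduce. For the exact one-sided test against 0.25 at n = 143, the critical value is 45 (actual level 0.048).

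**2. Node-positive patients.**
- At the 27% prevalence of section 3: 0.27 × 143 = 38.6.
- After removing USgFNAC-positive patients (sensitivity 15.4%): (0.27 − 0.0416)/(1 − 0.0416) = 0.238, and 0.238 × 143 = 34.1.

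**3. Candidates (section 8.1.2).** 6 SUV metrics + about 2 × 5 = 10 ratios = 16 quantitative candidates. With 5 morphology features this is 21, before the two visual scales and any combinations.

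**4. Simulation.** The AUCs, the correlations between markers (0.5 and 0.8) and the selection rules are assumptions of this review; the protocol gives none. All candidates are continuous and binormal, with n = 143. True PPV = π·S(t−d) / [π·S(t−d) + (1−π)·S(t)], where π is prevalence, t the chosen cut-off, S the upper normal tail and d = √2·Φ⁻¹(AUC).

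*Rule A: largest PET-positive share with apparent PPV of at least 0.70 and at least 10 positives; π = 0.27.* Markers are calibrated so that a true PPV of 0.70 is attained at a true share of exactly 0.25 (AUC 0.878).

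| Candidates | PPV apparent | PPV true | Share apparent | P(at least 45/143) |
|---|---|---|---|---|
| 1 | 0.71 | 0.70 | 0.25 | 0.19–0.21 |
| 6 | 0.71 | 0.65–0.66 | 0.29–0.30 | 0.38–0.42 |
| 16 | 0.71 | 0.64–0.65 | 0.31–0.32 | 0.46–0.52 |

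- The PPV excess with 6 to 16 candidates is about 5 to 7 points.
- With weaker markers (AUC 0.65–0.75, 6–16 candidates, only samples in which the rule could be met), apparent PPV is 0.71 and true PPV 0.48–0.61.

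*Rule B: highest PPV above a minimum share; 21 candidates, AUC 0.70, π = 0.238.*

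| Minimum share | PPV apparent | PPV true | Excess |
|---|---|---|---|
| 25% | 0.51–0.53 | 0.42 | 9–11 points |
| 10% | 0.68–0.71 | about 0.51 | 17–20 points |

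**5. What is biased and what is not.**
- Raw PET-positive share at the chosen cut-off, apparent against true: 0.294 against 0.292 (rule A, 6 candidates, correlation 0.8), and about 0.26 against 0.26 (rule B, 25% minimum). Nearly unbiased.
- True positives per patient, that is, positive SLNBs avoided: 0.21 against 0.19 (rule A, 6 candidates), and 0.13–0.14 against 0.11 (rule B, 25% minimum).
- Reaching 45/143: 38–52% of samples under rule A with 6–16 candidates, although only 0.25 is attainable at PPV 0.70; 0–3% under rule B at AUC 0.70.

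**6. Meaning for unnecessary dissections.** With 47 PET-positive patients, PPV 0.70 implies 47 × 0.30 = 14. A true PPV 5 to 7 points lower implies 47 × 0.35 = 16.5 to 47 × 0.37 = 17.4.

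**7. How much resampling recovers.** Rule A, 6 candidates, correlation 0.8: apparent PPV 0.707, bootstrap-corrected 0.681, true 0.665. The correction removes 0.026 of 0.042, about three fifths.

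**The case against.** The strongest reply is that this is a development cohort. Section 3 keeps PET/CT results out of surgical planning, so no participant is managed by the rule; the protocol raises the bias itself and uses LASSO; and internal validation is often left to an SAP, which may exist. Much of this stands. It lowers the severity, and absence of a correction can be claimed only for this document. It does not remove the point, because the protocol ties its primary endpoint to data-selected criteria, names the bias and leaves it open.

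The magnitudes are also open to challenge. The protocol asks for high PPV with tolerable sensitivity, not maximum PPV. A true PPV of 0.42 is far from the planning value of 0.70. Shape and low density are categorical, the two visual scales allow only four cut-offs each, and the Hopkins scale already exists. Section 3 also plans readings before new criteria are set, which are not optimised on the data. These are fair grounds for giving a range and for writing that results can be expected to be optimistic, not that they must be.

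A reader might infer more: that the primary SLNB reduction is itself biased upward, and that the test against 0.25 loses its 5% level. The documents do not support that in general. Section 4.4 derives the reduction as the PET-positive share, which is nearly unbiased at a given cut-off. The comparison with 0.25 appears only in the sample-size section; section 10.1 merely calculates the reduction per criterion, and nothing says the best one is carried into a test. Whether the level holds depends on a selection rule that the protocol does not state.

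**Conclusion.** The point holds for PPV and for results that count true or false positives: positive SLNBs avoided, unnecessary neck dissections, and the cost scenarios built on them. On average these can be expected to look too favourable, and intervals computed as described ignore the selection.

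The size is conditional: about 5 to 7 PPV points if the markers are strong enough to deliver the planned PPV of 0.70, about 9 to 20 points with 21 candidates of AUC 0.70, and close to none with a single strong marker. AUC, correlation and selection rule are assumed in each case. For SLNB reduction, what is overstated is the reduction attainable at the claimed PPV, not the raw PET-positive share. This should be fixed; it does not invalidate the design.

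**What to change.** Add to sections 10.1 and 10.2:

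- The whole procedure (imputation, LASSO, choice of criterion, choice of cut-off) is repeated within patient-level bootstrap samples or nested cross-validation.
- Optimism-corrected PPV, sensitivity and SLNB reduction based on true positives, with intervals from that resampling, are the main results. Apparent values stand beside them.
- Any formal comparison with 0.25 uses one criterion and cut-off fixed before PET/CT scores are linked to the reference-standard results.
- All other criteria are labelled exploratory development results pending external validation, because resampling removes only part of the bias.

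The numerical selection rule (the PPV sought and the sensitivity tolerated) has to be written down as well, since the procedure cannot be repeated in resamples without it.

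The cost is analysis programming and a less favourable reported PPV. No extra patients or procedures are needed.
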